## Abstract

**Background:**

Cardiac catheterization has opened an innovative treatment field for cardiac disease; this treatment is becoming the most popular approach for pediatric congenital heart disease (CHD) and has led to a significant growth in the number of children with cardiac catheterization. Unfortunately, based on evidence, it has been demonstrated that the majority of children with CHD are at an increased risk of “non-cardiac” problems. Effective exercise therapy could improve their functional status significantly. As studies identifying the efficacy of exercise therapy are rare in this field, the aims of this study are to (1) identify the efficacy of a home-based exercise program to improve the motor function of children with CHD with cardiac catheterization, (2) reduce parental anxiety and parenting burden, and (3) improve the quality of life for parents whose children are diagnosed with CHD with cardiac catheterization through the program.

**Methods/design:**

A total of 300 children who will perform a cardiac catheterization will be randomly assigned to two groups: a home-based intervention group and a control group. The home-based intervention group will carry out a home-based exercise program, and the control group will receive only home-based exercise education. Assessments will be undertaken before catheterization and at 1, 3, and 6 months after catheterization. Motor ability quotients will be assessed as the primary outcomes. The modified Ross score, cardiac function, speed of sound at the tibia, functional independence of the children, anxiety, quality of life, and caregiver burden of their parents or the main caregivers will be the secondary outcome measurements.

**Discussion:**

The proposed prospective randomized controlled trial will evaluate the efficiency of a home-based exercise program for children with CHD with cardiac catheterization. We anticipate that the home-based exercise program may represent a valuable and efficient intervention for children with CHD and their families.

**Trial registration:**

http://www.chictr.org.cn/ on: ChiCTR-IOR-16007762. Registered on 13 January 2016.

**Electronic supplementary material:**

The online version of this article (doi:10.1186/s13063-016-1773-7) contains supplementary material, which is available to authorized users.

## Background

Congenital heart disease (CHD) is one of the most common structural abnormalities, occurring in 9 of every 1000 live births [1, 2]. Over the last three decades, dramatic changes have occurred in pediatric cardiac catheterization, and cardiac catheterization is now the main procedure for pediatric cardiac disease. In comparison with traditional cardiac surgical procedures (open heart surgery), therapeutic cardiac catheterization has several advantages, including being simpler and safer, and it is associated with an improved outcome [3]. Hence, pediatric therapeutic cardiac catheterization has increased recently because of numerous innovative catheter techniques, the increased number of persons and centers using these techniques, and the increased number of lesion types thought to be amenable to catheter therapy. It has been considered as the regular procedure clinically in dealing with patent ductus arteriosus, pulmonary stenosis, ventricular septal defect, and atrial septal defect [4].

Progress in medical diagnosis and new surgical techniques imply that the majority of children with complex CHD (80%) now enter adulthood successfully [5–7]. With increased survival rates, emerging evidence has highlighted that “non-cardiac” problems have increased rapidly in survivors [6, 8]. Studies have demonstrated that abnormal hemodynamics during fetal gestation and hypoxia in utero might play an important role in the risk of long-term adverse neurological outcomes in children with critical CHD [9, 10]. A distinctive pattern of neurodevelopmental and behavioral impairments has been noticed over the years; these are characterized by delayed motor development, cognitive impairments, and other abnormal growth [11, 12]. Many school-aged survivors adapt poorly to their school life because of low physical activity levels and poor academic performance, and these problems may persist into young adulthood, leading to a low quality of life for these children and their families [13].

Motor delays are common in children with CHD because of various reasons. Studies demonstrate that cardiac problems are not the only reason responsible for development delays [11, 14–16]; overprotection of parents or main caregivers is also a factor. Parents are the most concerned caregivers for their children, and overprotection of children with CHD has been observed with most parents and teachers. These attitudes and the anxiety of overprotective parents might restrict the physical activity of their children and reduce their children’s exposure to their peers, and this, in turn, might influence the social competence and motor development of these children. As a result, children may develop a sedentary lifestyle, and this may lead to increased risks of additional cardiovascular diseases and complications [17]. Without intervention, these development deficits may persist into adolescence and adulthood [18]. Mothers of children with CHD are more concerned and anxious about their children’s behaviors than parents of children without such health issues [19]. They often exaggerate the risk of adverse events or medical prognoses of CHD, and they may underestimate the adaptability of their children. The consequence of such overprotection may be reduced physical, emotional, psychosocial, or cognitive functioning in their children [11, 20].

A few studies have developed interventions to improve growth development in children with CHD, but there is still limited evidence in the literature to support the potential benefits of rehabilitation for these children [21–25]. Only one study implemented a home-based training program for 20 toddlers, aged 12 to 26 months, after either a superior cardiopulmonary connection procedure or an arterial switch operation. The study revealed that a home-based training program could improve motor abilities and increase children’s rates of development to age-appropriate norms [25]. But these studies focus on complex CHD. Even though cardiac catheterization is a minimally invasive procedure, it causes damage to the body; moreover, the patients are very young, with poor psychology and compliance, which make post-surgery management difficult. It is reported that a better inpatient environment with enough emotional support for the parents during the pre- and post-procedure phase, as well as exercise therapy for the children post-procedure, could relieve pain and reduce complications [26]. Overall, little research relates to growth in the development of therapeutic intervention for CHD with cardiac catheterization.

This parallel randomized controlled trial aims to evaluate the efficacy of a home-based exercise program and whether it could improve the motor abilities of children with CHD with cardiac catheterization, reduce parental anxiety and parenting burden, and improve the quality of life for the children’s parents through the program, which may represent a valuable and efficient intervention for children with CHD and their families.

## Methods/design

### Aims

The aims of this research study are as follows:To evaluate whether a home-based exercise program may improve motor abilities in CHD children with cardiac catheterizationTo identify whether a home-based exercise program may reduce parental anxiety and caregiver burden and promote parents’ quality of life.

### Study design

Children with CHD who are planning to perform a cardiac catheterization procedure will be recruited from the Department of Pediatric Cardiology, Xinhua Hospital affiliated to Shanghai Jiao Tong University School of Medicine, China.

The study will be implemented at the Shanghai Jiao Tong University School of Medicine. Before participation in the study, parents/legal guardians will be asked to sign a written informed consent. First, patients who meet the inclusion criteria will be recruited for the study through echocardiography results. Second, patients will undergo baseline evaluations including motor abilities, cardiac function, modified Ross score, sound of speed at the tibia, and functional independence level, and their parents will complete three questionnaires about their anxiety levels, quality of life, and caregivers’ burden. Children with CHD will be allocated by a physician using computer-generated block randomization into two groups: an intervention group and a control group after the catheterization process. The allocations will be concealed in sequentially numbered, opaque, sealed envelopes through a signature across the sealing point. A trained research assistant, who will be blinded to the allocation, will enroll patients and assign them to interventions. All evaluations will be carried out by the evaluation team. Another team, composed of experienced pediatric physiotherapists, will teach parents the home-based exercises, remind them to perform the exercises, and provide valuable information about the details of the exercises. The evaluation team will be blinded in this program; however, the intervention team will not be blinded, as they must communicate with parents and offer informed consent in order to obtain the parents’ signatures. The intervention group will receive a home-based exercise program, while the control group will only receive home-based education (see Fig. 1). All children and parents will be evaluated by the trained evaluation team before the procedure and 1, 3, and 6 months after the cardiac catheterization. Micro Message Public Platform dissemination and collaboration with staff of the Department of Pediatric Cardiology was established to facilitate enrollment to reach the target sample size. All parents will be added into a CHD group of the Micro Message Platform created by the intervention team to remind them to bring their children for clinic visits in order to promote patient retention.

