### Sample measurement

GPower 3.1.9.2 will be used to perform the power calculations. The motor quotient of the PDMS-2 will be our primary outcome measurement.

The results of our pilot study showed that after 6 months of intervention, the motor quotient of the intervention group with patent ductus arteriosus on average was (94.33 ± 11.29), and that of the control group was (84.67 ± 6.11); therefore, the effect size was 1.06. Thus, as the α will be 0.05 and the β will be 0.05, each group should recruit 24 patients. Considering 10% potential attrition, 27 patients in each group with patent ductus arteriosus will be recruited.

The motor quotient of the intervention group with pulmonary stenosis on average after 6 months of intervention was (101.00 ± 9.90), and that of the control group was (89.00 ± 1.41); therefore, the effect size was 1.70. Thus, as the α will be 0.05 and the β will be 0.05, each group should recruit 11 patients. Considering 10% potential attrition, 13 patients in each group with pulmonary stenosis will be recruited.

The motor quotient of the intervention group with ventricular septal defect on average after 6 months of intervention was (95.00 ± 8.54), and that of the control group was (90.50 ± 7.78); therefore, the effect size was 0.55. Thus, as the α will be 0.05 and the β will be 0.05, each group should recruit 87 patients. Considering 10% potential attrition, 96 patients in each group with ventricular septal defect will be recruited.

The motor quotient of the intervention group with atrial septal defect on average after 6 months of intervention was (99.67 ± 5.43), and that of the control group was (90.80 ± 5.72); therefore, the effect size was 1.59. Thus, as the α will be 0.05 and the β will be 0.05, each group should recruit 12 patients. Considering 10% potential attrition, 14 patients in each group with atrial septal defect will be recruited.

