### Strengths and limitations

The first strength of our study is that it will be the first randomized controlled trial that focuses on home-based exercise for young children with CHD and cardiac catheterization. Second, except for the important elements of cardiac function, our study focuses more on growth development at an early stage for children with CHD. Third, we used GPower 3.1.9.2 software for the sample calculation to ensure its scientific validity. Fourth, our study will last for 6 months, with three re-evaluations, in order to update the patients’ recovery and development status in time. Fifth, our study develops a detailed and individual home-based exercise program for each patient, and provides a one-on-one guide for the parents, until they master the skills. Moreover, there is a close home-based monitoring process, which could ensure the quality of implementation of the home-based exercise program to a certain extent. Sixth, our intervention will not solely focus on the children, as their parents will also be educated in home-based exercise and other appropriate educational and care guidelines for children with CHD.

Several limitations exist in our trial: (1) the age of subjects is limited to 0 to 5 years; (2) we only recruit patients with cardiac catheterization for our trial; we will not group the children according to their specific CHD subtypes or the treatment approach to CHD; (3) we will not evaluate language and speech development or cognitive development directly, only motor development; thus, our trial cannot be used as a comprehensive evaluation of all types of home-based exercise programs for CHD children with cardiac catheterization; and (4) our study includes a short follow-up duration of 6 months.

In conclusion, our study design for delayed motor development of CHD children with cardiac catheterization developed a home-based exercise program as the main intervention approach after the procedure. It is crucial to address whether a home-based exercise program could improve the patients’ motor abilities and improve parental anxiety, burden, and quality of life. The findings will be beneficial for children with CHD and their families, research collaborators, physicians, and the general public.

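### The sample size fixes numbers per arm within four CHD subtypes, but the randomisation as described is not stratified by subtype, so those cell sizes are left to chance; the allocation roles also conflict

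*Protocol article*

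**What the plan says.** All references are to the protocol article.

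**Sample size.** Sample measurement does four separate calculations, one per subtype, each giving a number per arm. For patent ductus arteriosus (PDA) it says "as the α will be 0.05 and the β will be 0.05, each group should recruit 24 patients", raised to 27 for attrition. For pulmonary stenosis (PS) it ends: "Considering 10% potential attrition, 13 patients in each group with pulmonary stenosis will be recruited". Ventricular septal defect (VSD) gets 96 per arm and atrial septal defect (ASD) 14. The Abstract gives the overall size: "A total of 300 children who will perform a cardiac catheterization will be randomly assigned to two groups".

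**Randomisation.** Study design says: "Children with CHD will be allocated by a physician using computer-generated block randomization into two groups". It names no stratification factor and no block size, and places allocation after catheterisation. Strengths and limitations adds: "we will not group the children according to their specific CHD subtypes or the treatment approach to CHD".

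**Roles.** Study design specifies concealment: "The allocations will be concealed in sequentially numbered, opaque, sealed envelopes through a signature across the sealing point". The next sentence reads: "A trained research assistant, who will be blinded to the allocation, will enroll patients and assign them to interventions". Later it says that "the intervention team will not be blinded, as they must communicate with parents and offer informed consent".

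**The concern.** A number per arm within each subtype can be guaranteed only if allocation is made within each subtype. The text describes blocks that balance the two arms overall, and it disclaims grouping by subtype. Yet the total of 300 is nothing more than the sum of the subtype numbers. The sections therefore describe different designs.

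At stake are the stated cell sizes and balance on a factor that may be prognostic: pilot control means run from 84.67 (PDA) to 90.80 (ASD).

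The second issue is who does what. Someone who assigns a child to an arm cannot stay unaware of that child's arm, and two roles (physician and research assistant) are each said to allocate. The team that delivers the programme, and so knows past assignments, is also involved in consent. That is a possible route to selection bias at a single recruiting department.

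**Working it through.** **1. The plan's own figures.** The inputs are the pilot means and SDs in Sample measurement, with α = 0.05 and β = 0.05. The effect size is d = (m₁ − m₂)/√((s₁² + s₂²)/2). For PDA, d = 9.66/√((11.29² + 6.11²)/2) = 9.66/9.08 = 1.064. The sample size comes from a two-sided two-sample t test (noncentral t, power 0.95); the article does not state sidedness, but two-sided reproduces its numbers.

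| Subtype | d | n per arm, recomputed | n per arm, stated | n/0.9, rounded up | Stated after attrition |
|---|---|---|---|---|---|
| PDA | 1.064 | 24 | 24 | 27 | 27 |
| PS | 1.697 | 11 | 11 | 13 | 13 |
| VSD | 0.551 | 87 | 87 | 97 | 96 |
| ASD | 1.590 | 12 | 12 | 14 | 14 |

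The VSD figure of 96 equals 87 × 1.1 rounded up; the one-child difference is immaterial. The sum is 27 + 13 + 96 + 14 = 150 per arm, and 2 × 150 = 300. The stated numbers reproduce.

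**2. What unstratified blocks deliver.** Take subtype totals T of 54, 26, 192 and 28, arrival order unrelated to subtype, and complete blocks giving 150 per arm. The count X of a subtype in one arm is then hypergeometric:

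P(X = x) = C(T, x)·C(300 − T, 150 − x)/C(300, 150).

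Block size drops out. Simulations of 20,000 trials each with blocks of 2, 4, 6 and 10 agree.

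- All four numbers met exactly: C(54,27)·C(26,13)·C(192,96)·C(28,14)/C(300,150) = 0.0031, about 0.3%.
- One arm below the pre-attrition n, before any dropout (X < n or X > T − n): PDA 0.29, PS 0.30, VSD 0.02, ASD 0.32.
- At least one subtype short: 1 − 0.338 = 0.662, about 66%.
- 95% range for one arm: PDA 20–34, PS 8–18, VSD 88–104, ASD 9–19.

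**3. Cost in power.** This uses the stated d, a noncentral t with noncentrality d√(n₁n₂/(n₁ + n₂)), a common SD, and 10% loss in each arm.

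| Subtype | Uneven split | After loss | Power | Balanced after loss | Power |
|---|---|---|---|---|---|
| PDA | 20:34 | 18:31 | 0.939 | 24:24 | 0.949 |
| PS | 8:18 | 7:16 | 0.947 | 12:12 | 0.978 |
| VSD | 82:110 | 74:99 | 0.945 | 86:86 | 0.948 |
| ASD | 9:19 | 8:17 | 0.944 | 13:13 | 0.973 |

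The largest drop is 0.978 − 0.947 = 0.031. The VSD split is wider than its 95% range above, so that row is pessimistic.

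**4. Noise from chance imbalance.** The weighted mean of the pilot control means is (54×84.67 + 26×89.00 + 192×90.50 + 28×90.80)/300 = 89.35, with between-subtype variance 5.00. The SD of the shift in the overall arm difference is √(5.00 × 300/299 × 2/150) = 0.26 quotient points. Pilot differences run from 4.5 (VSD) to 12 (PS).

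**5. Predictability at consent.** Assume blocks of 4, every earlier assignment known, and no consented child awaiting allocation.

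- Certain assignments: (0 + 0 + 1/3 + 1)/4 = 33%.
- Correct best guesses: (1/2 + 2/3 + 2/3 + 1)/4 = 71%.

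With one consented child still unallocated, these become (0 + 0 + 0 + 1/3)/4 = 8% and (1/2 + 1/2 + 2/3 + 2/3)/4 = 58%. With two pending they are 0% and 54%; with three, 0% and 50%.

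**The case against.** **Absence of stratification is partly an inference.** A condensed article may omit the factor. But the Strengths and limitations sentence points the same way, and the randomisation scheme cannot be supplied later by an analysis plan. That sentence could also mean that no subtype comparison is intended, which would make the per-arm numbers matter less. Sample measurement nevertheless says those numbers will be recruited, so the sections still need reconciling.

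**The harm is modest.** This stands. Missing a cell by a few children costs little power, and the noise added to the overall comparison is small. A reader might infer that the trial would be underpowered; the figures do not support that.

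**The shortfall is easily overstated.** Treating every child as an independent coin toss gives only a 24% chance that all four minima are met. Blocks fix the arm totals, so that model is wrong here; the figure is about 34%, with a VSD shortfall of 2%.

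**Concealment.** A reader might infer that concealment fails. The article does not show this. It specifies a standard envelope method, and describing the assistant as blinded can be read as unaware of the next assignment. The physician and assistant could be list-holder and enroller. What stands is that the wording does not say so.

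**Predictability.** The 33% and 71% are a worst case under an assumed block size. Allocation follows catheterisation, so some consented children may be unallocated when the next family is approached, and the figures then fall quickly.

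**Conclusion.** The main point holds. Sample measurement, Study design and Strengths and limitations do not describe one design, and the stated cell sizes are left to chance: about 0.3% of trials meet all four exactly, and about 66% have at least one arm short before dropout. These figures assume no stratification, subtype totals of 54/26/192/28 and arrival order unrelated to subtype; they do not depend on block size.

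The consequence is undelivered cell counts and avoidable imbalance, with a power loss of at most about 3 points per subtype. That limit assumes a common SD in both arms. It does not cover arm SDs as unequal as the PS pilot's (9.90 and 1.41).

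The secondary point holds as a conflict of roles, with an unblinded team involved in consent. The resulting risk of selection bias cannot be sized, because neither block size nor the number of children awaiting allocation is given. The change should be made because it is cheap and, with recruitment ongoing according to Trial status, still possible.

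**What to change.** 1. Stratify the remaining allocations by the four subtypes: one envelope series per subtype, with randomly varied block sizes. Record the date of the change; allocations already made stand.
2. Add subtype to the covariance model, which at present is motivated by age alone. This also adjusts for imbalance among children already allocated.
3. Reconcile Study design, Sample measurement and Strengths and limitations, stating whether the subtype numbers are recruitment targets per arm.
4. State who generates the list. Have consent taken by existing staff who do not know past assignments. Have the envelope opened only once baseline assessment and catheterisation are logged, by existing staff who neither recruit nor assess outcomes. State who is blinded, and from when.
5. If predictability is quoted, label it a worst case under an assumed block size with no consented child awaiting allocation.

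The cost is four envelope series in place of one, one more model term, and a reassignment of existing duties. No new staff or visits are needed.

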**Fig. 1 Fig1:**
[figure not shown]
Flow diagram showing home-based exercise program for children with CHD following interventional cardiac catheterization

The intervention group will implement a home-based exercise program, while the control group will receive home-based exercise education. Both groups will continue with their routine activities, but they will not be able to attend any other formal exercise program.

This study design follows the SPIRIT guidelines (see Fig. 2 and Additional files 1 and 2).

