### Intervention

The home-based exercise program will consist of home-based exercise education, home-based exercise, and home-based exercise supervision.Home-based exercise education: The intervention team will explain the results of the developmental tests of their children to each family and emphasize the importance of home-based exercise for their children. Then, parents will receive a home-based physical activity brochure, and follow a Micro Message Public Platform that will share various forms of CHD knowledge twice monthly including exercise, education materials, and general care of children with CHD. It will also provide the exercise guide and tools for outpatient appointments. Parents will be asked to take their children to perform daily outdoor activities.Home-based exercise: The home-based exercise program will be adopted from the motor activities program of Peabody Motor Development [27]. The home-based exercise program will be designed by the pediatric cardiologist, rehabilitation physician, and intervention team with input from the parents. The home-based exercise program will be individualized to each child’s developmental age, severity, and degree of developmental delay. The baseline assessment results will be used to identify age-appropriate skills that the children have not yet mastered. The exercise program will be designed so that parents can choose how to incorporate these activities into their daily schedules and preferred behaviors. First, a member of the intervention team will provide the parents with one-on-one rehabilitation program training until the parents master the skills. In addition, the parents will be given a home-based game reader and the Micro Message Public Platform to guide them. At least one of the children’s parents will be asked to complete the entire exercise program, and the rest of the family members must agree and support the home-based exercise program. The intervention team will maintain contact with the parents by phone to provide the exercise guide.

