#### Compliance supervision

The intervention team will remind parents to carry out the exercise program and monitor each child’s progress through a Micro Message Public Platform or phone call one or two times weekly, and will also help them schedule rehabilitation evaluation appointments.

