### Control group

The intervention team will explain the children’s evaluation results and share home-based exercise education with parents at baseline assessments. Home-based physical activity education will be given to the parents, but they will not receive the rehabilitation guide.

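### One parent messaging group for both arms, and inconsistent text on whether controls can reach the exercise guide, leave an unguarded contamination route of unknown size

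*Protocol article*

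**What the plan says.** Four places in the protocol article bear on this.

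- **Study design.** "All parents will be added into a CHD group of the Micro Message Platform created by the intervention team", with the stated purpose "to remind them to bring their children for clinic visits in order to promote patient retention". The same section says the intervention team is not blinded. It also says the public platform was used to help enrolment.
- **Intervention.** The programme has three components: education, exercise and supervision. Under education, parents are to "follow a Micro Message Public Platform that will share various forms of CHD knowledge twice monthly including exercise, education materials", and of that platform the text adds: "It will also provide the exercise guide and tools for outpatient appointments". Under the exercise component the platform appears again: "the parents will be given a home-based game reader and the Micro Message Public Platform to guide them".
- **Compliance supervision.** The intervention team will remind parents to exercise and "monitor each child’s progress through a Micro Message Public Platform or phone call one or two times weekly".
- **Control arm.** The text below Fig. 1 says "the control group will receive home-based exercise education", and the Abstract says the same. The Control group section says: "Home-based physical activity education will be given to the parents, but they will not receive the rehabilitation guide".

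The article does not state platform or group access by arm, set rules for what may be posted in the shared group, or record exercise done by control families. Its one restriction on exercise outside the protocol, in both arms, concerns other formal programmes.

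**The concern.** The trial compares an exercise programme with education alone, so the comparator must be clear and the arms kept apart. Two features work against this.

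First, the article is inconsistent about the comparator. Read literally, the education component contains a platform that carries the exercise guide. Controls receive a component of that name but not the rehabilitation guide. The article does not say whether the exercise guide and the rehabilitation guide are the same thing.

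Second, parents of both arms meet in one group created by the people who teach the exercises, and no safeguard is described.

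If control families take up the exercises, the difference in motor quotient shrinks. More children would restore power but would not remove that bias. With no record of control-arm exercise, a small or null difference would be harder to attribute to the programme itself.

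**Working it through.** **1. The plan's own sample sizes (Sample measurement).** Inputs are the pilot means and standard deviations, α = 0.05 and β = 0.05. The formula is d = (mean₁ − mean₂)/√((s₁² + s₂²)/2), followed by a two-sample t test (noncentral t), 1:1. Sidedness is not stated. Two-sided testing reproduces the plan; one-sided would give 20, 9, 73 and 10.

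| Defect | d recomputed (stated) | n per group recomputed (stated) |
|---|---|---|
| Patent ductus arteriosus | 1.064 (1.06) | 24 (24) |
| Pulmonary stenosis | 1.697 (1.70) | 11 (11) |
| Ventricular septal defect | 0.551 (0.55) | 87 (87) |
| Atrial septal defect | 1.591 (1.59) | 12 (12) |

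After attrition the plan has 27 + 13 + 96 + 14 = 150 per group, 300 in total. The only allowance is 10% attrition; there is none for dilution.

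**2. Dilution model.** If a share c of the effect is lost, the expected difference is (1 − c) times the planned one, so d becomes d(1 − c), with the standard deviation held fixed. A 20% loss could mean 20% of control families gaining the full effect, or 40% gaining half of it (0.40 × 0.50 = 0.20). The article gives no value for c; 10%, 20% and 30% are assumptions.

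**3. Effect on the estimate.** For ventricular septal defect the pilot difference is 95.00 − 90.50 = 4.50 points. It would become 4.05, 3.60 and 3.15 points at c = 10%, 20% and 30%.

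**4. Effect on power.** The noncentrality is d(1 − c)·√(n/2), two-sided 0.05. Two settings are shown: the ventricular septal defect calculation (n = 87), and all defects pooled at 150 × 0.9 = 135 evaluable per arm with the smallest d, 0.55, used throughout.

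| Loss c (assumed) | d(1 − c) | Power, n = 87 per arm | Power, n = 135 per arm |
|---|---|---|---|
| 0 | 0.550 | 95% | 99% |
| 10% | 0.495 | 90% | 98% |
| 20% | 0.440 | 82% | 95% |
| 30% | 0.385 | 71% | 88% |

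At the same losses the other three calculations behave similarly: 90%, 82% and 71% for patent ductus arteriosus; 93%, 86% and 76% for pulmonary stenosis; 92%, 85% and 74% for atrial septal defect. Restoring 95% power for ventricular septal defect would take 108, 136 or 177 evaluable children per group instead of 87.

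**The case against.** The case for the plan has real force.

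- **The shared group may be a separate channel.** Its only stated purpose is visit reminders, and the article never says exercise material is posted there. This stands. A reader might infer that control parents will see the exercises discussed, but the text does not say so.
- **Control access to the public platform is an inference.** It rests on the shared label for the education component. The Control group section describes education shared at baseline and does not mention the platform. This also stands, so the article does not establish that controls receive the guide. Equally, nothing restricts the platform by arm, and its use for enrolment suggests it was not closed to one arm.
- **Much of the programme cannot leak this way.** One-on-one training, the individualised programme and weekly supervision are described only for the intervention arm, and the game reader is listed separately from the platform. Control uptake would therefore probably be partial. That limits the size of any dilution but not its direction.
- **The single-defect power figures may overstate the loss.** Strengths and limitations says children will not be grouped by subtype, and pooled power holds up well at modest dilution. This stands, and is why both settings are shown. A reader might conclude that a null result would be uninterpretable; at 10% to 20% loss the pooled figures do not support that.
- **The article is condensed.** Group moderation and account permissions may be set out in the full protocol. That could settle the access question, but the article's own wording on the comparator would still need reconciling.

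**Conclusion.** The concern holds as an unguarded contamination route of unknown size, together with inconsistent text on what the control arm can reach. It does not hold as a claim that the plan builds contamination in: no rate is given, and control access to the guide is inferred rather than stated.

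The direction is clear, since control uptake of a beneficial programme pulls the difference toward zero. The consequence depends on the analysis. A 20% loss would matter for the separate defect calculations on which the sample size is built (82% to 86% power instead of 95%) but would leave the pooled comparison at about 95%. At 30% the pooled figure is about 88%. These figures rest on the assumed losses, an unchanged standard deviation, no covariate adjustment and, for the pooled case, d = 0.55 in every defect. The change is worth making because it is nearly free.

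**What to change.** 1. Send visit reminders one to one, or run two arm-specific groups with no shared membership.
2. Place the exercise guide and exercise posts on an account open only to the intervention arm.
3. Reword the Intervention and Control group sections so that the education given to both arms excludes the guide, and say whether the exercise guide and the rehabilitation guide are the same document.
4. At the 1, 3 and 6 month visits, ask control families whether they used the guide or the exercises, so that any dilution can be described. Someone outside the blinded evaluation team should ask, because the answers could reveal the arm.

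The cost is a second group or account to run and one added question per visit. Trial status says recruitment is ongoing, so separation would protect later enrolments only, while the question can start at once for families still in follow-up. If the full protocol already separates access by arm, items 3 and 4 remain.
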